**Mandatory requirement**			
Participant has accessed and completed 10 (66.66%) or more sections from the intervention (including goal setting and action planning section)	Participant has accessed and completed more than 5 but less than 10 of the sections from the intervention (including goal setting and action planning section)	Participant has accessed and completed fewer than 5 (33.33%) of the sections in the intervention **or** has not completed the goal and action planning section	Participant does not fulfil the necessary conditions to be considered as **Limited compliant**

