### Intervention

The FACT self-management intervention is based on the common-sense model of self-regulation [23] and consists of four structured modules covering aspects of fatigue management, including (i) About fatigue; (ii) Managing your energy with the 5 Ps (Priorities, Pacing, Planning, Permission, Position); (iii) Strategies for everyday life; and (iv) Goal setting and making plans. The intervention is separated into 16 sections and includes information in the form of both videos and text, activities, as well as patient stories. It is available via a website with all information and activities available to download and accessible in multi-formats (infographics, videos, printable and editable documents). A printed booklet will also be available according to patient preferences.

Patients will be encouraged but not required to move through the topics in the order presented and will be able to use the intervention at their own pace, repeating any topics if desired. As described in “Trial Design”, participants will receive a 30-min supportive phone or video call with an HCP from the ICU follow-up team at three months post-discharge. During this call, the HCP will assist with goal setting and action planning. To ensure consistency and quality of delivery, HCPs will attend an online training session and follow a defined protocol. In addition, a manual for research delivery nurses has been developed, which includes a clear timeline and action checklist to guide screening, recruitment, and participant follow-up. To support the delivery of the intervention, supportive call materials have also been prepared, including a supportive phone call structure and example scripts to help HCPs conduct the phone calls effectively and maintain fidelity to the intervention framework.

The control arm will receive usual care across all the research sites; existing inpatient ICU follow-up services are offered. These include inpatient ICU follow-up services, and patients who were in ICU for more than 72 h are offered outpatient services three months after hospital discharge, where physical and psychological health outcomes are evaluated. Where necessary, appropriate referrals and treatment plans are made. In addition, patients may also have access to generic information about recovery after critical illness available on a variety of websites (ICU Steps, criticalcarerecovery.com), which includes information about fatigue.

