
Additionally, to evaluate the acceptability and fidelity of the intervention will be evaluated using a combination of quantitative and qualitative methods six months after randomisation. Participants will complete the Theoretical Framework for Acceptability Questionnaire (TFAQ) [32] and the System Usability Scale (SUS) [5] to assess their perceptions of the intervention and the usability of the digital platform.

Theoretical Framework for Acceptability Questionnaire (TFAQ) [32]TFAQ Comprises: Section 1 (All participants) including 6 items covering affective attitude, burden, ethicality, self-efficacy, opportunity costs, and general acceptability and Section 2 (Intervention group only) including 8 items covering the same plus perceived effectiveness and intervention coherence Responses are on a 5-point Likert scale from 1 to 5.System Usability Scale (SUS) [5]The SUS contains 10 items measuring system usability. Responses range from 1 (“strongly disagree”) to 5 (“strongly agree”). Items alternate between positively and negatively worded statements. Question 2, 4, 6, 8, and 10 are reverse scoring.Digital analytics, including the completion of sections from the intervention website will be used to measure patterns of engagement with the intervention components. These data will be collected at the 6-month follow-up and will be included in the evaluation of compliance level.

To be more specific, participants in the intervention group will be evaluated for compliance based on four categories: high compliance, moderate compliance, limited compliance and non-compliance, as summarised in Table 2. Highly compliant participants are those who complete at least 10 sections (66.66% or more) of the intervention, receive the supportive phone call, and set a personal goal with an action plan. Moderately compliant participants complete between 6 and 9 sections of the intervention and fulfil at least one secondary requirement, such as receiving the supportive phone call or setting a personal goal with or without an action plan. Limited compliant participants complete fewer than 5 sections (33.33% or less) but meet at least one secondary requirement. Participants who do not satisfy the criteria for a given category will be classified in the next lower level of compliance, with non-compliant participants being those who fail to meet the criteria for limited compliance.

**Table 2 Tab2:** Details for compliance levels

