**Secondary requirements**			
**(Need to satisfy both or assessed as moderately compliant)**	**(Need to satisfy at least one or assessed as limited compliance)**	**(Need to satisfy at least one or assessed as non-compliant)**	
Participant has received the supportive phone call	Participant has received the supportive phone call	Participant has received the supportive phone call	Participant has not received the supportive phone call
Participant has set a personal goal and devised an action plan	Participant has set a personal goal (with or without an action plan)	Participant has set a personal goal (with or without an action plan)	Participant has not set a goal or an action plan

In addition to quantitative measures, the acceptability of the intervention will be assessed through semi-structured interviews with participants to assess their adherence and provide further understanding of feasibility in the sixth month. Semi-structured interviews of health professionals are also included to evaluate HCPs’ perceptions and experiences of delivering support in this intervention. Topics will include affectivity, burden, ethicality, perceived effectiveness, intervention coherence, self-efficacy, opportunity costs, and general acceptability. These interviews will use a topic guide based on the theoretical constructs of acceptability [31].

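### The compliance classification uses percentages that fit 15 sections when the intervention has 16, and assigns exactly 5 completed sections to no count band

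*Protocol article*

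**What the plan says.** The Intervention section of the protocol article fixes the total: "The intervention is separated into 16 sections".

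The compliance rule appears twice, as a paragraph under Secondary outcome measures and as Table 2.

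- **High.** Table 2: "Participant has accessed and completed 10 (66.66%) or more sections from the intervention", with the goal-setting and action-planning section among them. The paragraph: "complete at least 10 sections (66.66% or more) of the intervention", plus the call and a goal with a plan, but no condition on the goal section.
- **Moderate.** Table 2: "more than 5 but less than 10 of the sections from the intervention", again with the goal section included. The paragraph gives 6 to 9 sections and is silent on the goal section. Both ask for at least one secondary requirement (the call, or a goal with or without a plan).
- **Limited.** The paragraph: "Limited compliant participants complete fewer than 5 sections (33.33% or less) but meet at least one secondary requirement". Table 2 uses the same strict limit, and adds a second way in: not having completed the goal section, whatever the count.
- **Step-down.** The paragraph: "Participants who do not satisfy the criteria for a given category will be classified in the next lower level of compliance". Non-compliant is then everyone who fails Limited. Table 2 puts the matching instruction above the High column's secondary requirements: "Need to satisfy both or assessed as moderately compliant".

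**The concern.** A four-level classification should place every participant in exactly one level, and doing more of the intervention should never lower the level. This rule appears to fail on both counts at 5 sections. Its percentages also do not belong to an intervention of the stated length, so count and percentage can give different answers for the same person.

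Adherence and fidelity form a stated secondary objective (Aims and objectives), and these four categories are how compliance is to be evaluated. As written, two analysts could code the same usage data differently. A choice made after seeing the data would be post hoc. The article spells the rule out in full, so this is not a detail it simply leaves to another document.

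**Working it through.** **Inputs.** Total sections 16 (Intervention); cut-offs 10 and 5 with 66.66% and 33.33% (Secondary outcome measures, Table 2); intervention arm 35 (70 randomised 1:1, Study design; 70/2 = 35).

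**Percentages.** Formula: sections completed / total.

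| Sections | of 15 | of 16 | Printed |
|---|---|---|---|
| 10 | 66.67% | 62.5% | 66.66% |
| 5 | 33.33% | 31.25% | 33.33% |

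The printed figures are reproduced only with 15 (66.66% is 66.67% truncated). On 16 sections, 0.6666 × 16 = 10.7, so a true two-thirds threshold is first met at 11 sections (68.75%). At the lower end, 0.3333 × 16 = 5.3, so one-third or less covers 0 to 5. At the printed precision it also covers 5 of 15. The paragraph's strict limit for Limited therefore excludes 5 while its own percentage includes it, on either total.

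**Count bands.** High is 10 and above, Moderate 6 to 9, Limited 0 to 4. The value 5 is in none of them.

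**Applying the rule to individual participants.**

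| Participant | Table 2, literal | Paragraph, by count | Paragraph, by percentage |
|---|---|---|---|
| 0 sections, call | Limited | Limited | Limited |
| 4 sections with goal section, call | Limited | Limited | Limited |
| 5 sections with goal section, call, goal, plan | Non-compliant | Non-compliant | Limited |
| 5 sections without goal section, call | Limited | Non-compliant | Limited |
| 6 sections with goal section, call | Moderate | Moderate | Moderate |
| 6 sections without goal section, call | Limited | Moderate | Moderate |
| 10 sections without goal section, call, goal, plan | Limited | High | not High (62.5% is below 66.66%) |

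Two results follow.

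1. In the Table 2 column, going from 4 to 5 sections with the goal section lowers the class from Limited to Non-compliant. Among people with 5 sections and the call, having completed the goal section rather than another one does the same. The rule is not monotone.
2. The sixth and last rows show that paragraph and table disagree on the goal section. Such participants can exist: a goal can be set with the healthcare professional during the call (Intervention), without the website section being completed.

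**Size.** One participant is 1/35 = 2.9 percentage points of the intervention arm. The documents do not say how many will finish on exactly 5 sections. If it were 1, 2 or 3, the shift would be 2.9, 5.7 or 8.6 points (2/35, 3/35).

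**The case against.** The strongest defence is that the counts are operative and the percentages are only glosses. Both texts agree that 10 sections qualifies as High by count. That stands: the percentage error gives no reason to move the High cut-off to 11.

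A second defence is that the intended reading at 5 can be guessed. The paragraph's percentage points to Limited. So does the Non-compliance column of Table 2, whose secondary rows describe someone with neither call nor goal, which does not fit a participant who has both. One could also read the step-down sentence as placing anyone who fails Moderate in Limited. This shows what was probably meant, but does not repair the rule: the same sentence makes anyone who fails Limited Non-compliant, and 5 fails the strict limit.

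Four stronger readings might be inferred, and the documents do not support them:

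- *Everyone with exactly 5 sections is Non-compliant.* Under Table 2 this needs the goal section to be among the 5. Otherwise the second route gives Limited once the call or a goal is present. The paragraph gives two answers.
- *Ten or more sections with one missed secondary requirement falls to Non-compliant, because Moderate is capped below 10.* The heading "Need to satisfy both or assessed as moderately compliant" and the step-down sentence assign that person to Moderate. The cap makes the cell untidy, but the destination is stated.
- *Compliance drives the decision to proceed.* Table 1 has two criteria, recruitment and retention with follow-up completion. Compliance is not among them.
- *Zero sections plus the call should not count as Limited.* The call is a core component and a printed booklet is offered, so credit without website sections is a legitimate design choice. It matters here only as the comparator that exposes the reversal at 5.

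**Conclusion.** The point holds in two places and for one mismatch. The printed percentages belong to 15 sections, not the stated 16. Exactly 5 sections has no count band, and read literally Table 2 then ranks a participant with 5 sections including the goal section, the call, a goal and a plan below one with no sections and the call. The paragraph and Table 2 also differ on whether the goal section is required for High and Moderate.

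The first result rests on 16 being the true section count. If it is really 15, the percentages are right apart from truncation and the Intervention section is wrong; the gap at 5 remains either way. The second rests on taking the strict count limit as written.

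The consequence is modest: about 2.9 percentage points per misplaced participant, in a descriptive secondary outcome. The component data (sections, call, goal, plan) allow reclassification. Randomisation, the primary outcome and the progression criteria are untouched. It should be corrected, but it does not threaten the trial.

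**What to change.** Use one rule in both places:

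1. Correct the percentages to 62.5% and 31.25%, or correct the section count in the Intervention section if 15 is right. Keep the count cut-offs of 10 and 6.
2. Define Limited as 5 or fewer sections, or goal section not completed, with at least one secondary requirement.
3. State in the Moderate cell that it also takes participants with 10 or more sections (goal section included) who do not meet both of High's secondary requirements but meet at least one of Moderate's. This writes down what the Table 2 heading already directs.
4. Put the goal-section condition for High and Moderate, and the alternative route into Limited, in the paragraph as well as the table, or remove them from both.

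With the Table 2 version of item 4, every participant with the call or a goal is at least Limited, and Non-compliant is exactly those with neither, as the last column of Table 2 describes. No step towards fuller use lowers the class.

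The cost is one reworded paragraph, one reworded table and the derivation code, with no new data. The wording is best settled before usage data are examined.

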**Secondary requirements**			
**(Need to satisfy both or assessed as moderately compliant)**	**(Need to satisfy at least one or assessed as limited compliance)**	**(Need to satisfy at least one or assessed as non-compliant)**	
Participant has received the supportive phone call	Participant has received the supportive phone call	Participant has received the supportive phone call	Participant has not received the supportive phone call
Participant has set a personal goal and devised an action plan	Participant has set a personal goal (with or without an action plan)	Participant has set a personal goal (with or without an action plan)	Participant has not set a goal or an action plan

In addition to quantitative measures, the acceptability of the intervention will be assessed through semi-structured interviews with participants to assess their adherence and provide further understanding of feasibility in the sixth month. Semi-structured interviews of health professionals are also included to evaluate HCPs’ perceptions and experiences of delivering support in this intervention. Topics will include affectivity, burden, ethicality, perceived effectiveness, intervention coherence, self-efficacy, opportunity costs, and general acceptability. These interviews will use a topic guide based on the theoretical constructs of acceptability [31].

### Data analysis

#### Quantitative

Assessments will be performed at baseline, three months, and six months post-randomisation to evaluate feasibility and acceptability. Descriptive statistics will be employed to summarise the baseline demographic and clinical characteristics of both groups. Categorical variables will be reported as frequencies, percentages, and 95% confidence intervals (CI). Continuous variables that are approximately normally distributed will be summarised as means with standard deviations (SD) and 95% CIs. Continuous variables that are non-normally distributed will be summarised using medians with interquartile ranges (IQR).

Feasibility outcomes (including recruitment and retention) will be analysed using descriptive statistics only, consistent with feasibility study methodology. These outcomes will be compared against the pre-specified progression criteria to determine whether they are practical and appropriate to proceed to a definitive RCT.

An analysis of data in the questionnaires will explore potential differences between the groups and whether there is a difference in the change between the groups before and after the intervention to assess the effectiveness of the intervention in reducing fatigue and improving overall quality of life.^1^ Analyses will be conducted based on intention-to-treat (ITT). As this is a small study, treatment effects are likely to have wide CIs and consequently inferences will be tentative and reported as such. Results will be reported in accordance with CONSORT extension to randomised pilot and feasibility trials [16]. A summary of outcome measures, data types, and analysis is listed in Table 3.

**Table 3 Tab3:**
[figure not shown]
Summary of data analysis plan

#### Qualitative

Qualitative data will be collected through semi-structured interviews, guided by a topic guide developed based on the theoretical constructs of acceptability [31]. These interviews will allow for an in-depth exploration of participants’ perceptions, experiences, and views regarding the intervention. The topic guide will ensure that key areas of interest are systematically addressed while allowing flexibility to follow up on emerging themes during the interviews.

The collected data will be analysed using the six-phase approach to thematic analysis as outlined by Braun and Clarke [4]. This method involves familiarisation with the data, generating initial codes, searching for themes, reviewing themes, defining and naming themes, and producing a final report. This rigorous and systematic approach will ensure that the analysis is comprehensive and provides a nuanced understanding of the qualitative data.

## Monitoring

### Patient and public involvement

The patient advisory group (PAG) consists of the patient co-applicants who will act as chair, the Patient and Public Involvement and Engagement (PPIE) lead researchers, and other patient and carer representatives. This group will meet alternate monthly for the duration of the trial. With support from the PPIE lead, the PAG will review recruitment materials, comment on data analysis, and advise on dissemination materials and strategies, comment on guidance arising from the study and assist in the completion of an impact log.

The PAG group includes people with fatigue after critical illness and HCPs working in critical care rehabilitation have been involved in the development of the intervention and planning of this trial. As part of an earlier study, seven people with fatigue after critical illness, one carer/family member, and seven HCPs co-produced the intervention, and four people with fatigue after critical illness used the draft intervention as part of user testing [7]. Six people with fatigue after critical illness and 4 HCPs have provided input into the development of the trial design and funding submission and reviewed trial documentation, including participant information sheets and invitations. The PPI group will continue to act in an advisory capacity throughout the trial.

### Administrative structures

The study will be monitored by the TMG, which includes the Chief Investigator, Principal Investigators (PIs), patient co-applicant, research team, and the trials unit team. The TMG will meet biweekly during the planning and set-up phases of the trial and every four weeks during the trial’s operational phase. The TMG will ensure adherence to agreed milestones and provide rapid responses to any issues that arise.

In addition to the TMG, the PAG and Clinical Advisory Group (CAG) will provide additional support to the trial. The PAG, chaired by patient co-applicants and supported by PPIE lead researchers and other patient and carer representatives, will meet every two months. Their role will include advising on recruitment materials, reviewing study outputs, contributing to dissemination plans, and supporting the documentation of the study’s impact. The CAG, composed of HCPs who work with patients recovering from critical illness, will meet quarterly to offer input on recruitment strategies, monitor study progress, and guide analysis, dissemination, and implementation processes.

These structured oversight mechanisms will ensure the trial’s progress is carefully monitored, with input from diverse stakeholders, including researchers, clinicians, and patient representatives.

## Ethics and dissemination

### Research ethics approval

Approval for this protocol was granted by the Health Research Authority (HRA) and the NHS Research Ethics Committee (REC) (IRAS ID 328471) on 5th December 2024. Any substantial amendments to the approved protocol or related documents will be submitted for further review and approval by the HRA, REC, and communicated to participating organisations and participants as required.

### Dissemination policy

The findings of this study will be disseminated through diverse channels to effectively reach various audiences. Academic and professional audiences will be engaged through peer-reviewed journal publications, conference presentations, and reports shared with professional organisations and NHS Trusts. Patients and advocacy groups will receive visual abstracts and summaries designed for accessibility, while the public will be reached via social media campaigns, podcasts, and university outreach. Policymakers will receive targeted reports to advocate for evidence-based interventions.

## Discussion

Fatigue after critical illness is a significant and under-recognised problem that profoundly impacts the recovery and quality of life of ICU survivors. Brown et al. [6] and Hosey et al. [20] highlight the urgent need for targeted interventions to address the pervasive and debilitating effects of post-ICU fatigue, emphasising the importance of bridging gaps in post-critical care rehabilitation services. Despite its prevalence, effective strategies to manage fatigue remain limited, underscoring the necessity of innovative, patient-centred approaches.

Findings from this feasibility study will inform the design of the full-scale randomised controlled trial by identifying the optimal conditions for both participant engagement and implementation. Specifically, the study will assess patients’ willingness to participate and determine the most appropriate timing for recruitment, including when survivors feel physically and emotionally ready, have rebuilt trust in healthcare interactions, and are less likely to be overburdened by other research commitments. It will also explore the capacity of research delivery nurses and HCPs at each local site, enabling optimisation of operational processes to ensure smooth collaboration and consistent delivery. Addressing these factors will be essential to enhance recruitment efficiency, support participant adherence, and ensure high-quality intervention delivery in the larger-scale trial.

